### Trial structure

The trial structure of the study is described in the Table 2. A specially trained nurse-tutor (NT) and physiotherapist (PT) screened the electronic patient boards every week at each rehabilitation hospital for eligible candidates for the study and checked their eligibility in terms of the inclusion and exclusion criteria with the study doctor. If any possible candidates had been admitted in the previous week the patients were informed verbally and in writing about the study by the study team. Before discharge from hospital to home (T0), all candidates underwent assessment of arterial blood gases and nutritional status by Body Mass Index (BMI). Then patients were also administered the following evaluations or scales:

**Table 2 Tab2:** Trial structure of the study

Activity/Assessment	Pre visit	T0	T1	T2
	During hospitalization	Visit 1	Visit 2	Visit 3
		Baseline (before discharge)	After 4 months	After 2 further months
Prescreening consent	X			
Consent Form		X		
Inclusion/Exclusion Form	X			
Arterial blood gases		X	X	
Body Mass Index (BMI)		X	X	
6MWT		X	X	X
MRC scale		X	X	X
Borg scale		X	X	X
Barthel Index		X	X	X
PASE		X	X	X
MLHFQ		X	X	X
CAT		X	X	X
Triage to assess the patient’s compliance to the rehabilitation program (only in the intervention group)			X	
Customer satisfaction (only in the intervention group)			X	

Evaluation of exercise capacity by the 6-min Walk Test (6MWT) [22]Assessment of dyspnea in activities of daily living (ADL) by the Medical Research Council (MRC) scale [23]Assessment of dyspnea and muscle fatigue in ADLs by the Borg scale [24] – patients were asked to report their own sensations referring to the previous dayEvaluation of disability by the Barthel Index [25]Indirect assessment of physical activity by the Physical Activity Scale for the Elderly (PASE) [26]Assessment of QoL by the Minnesota Living with Heart Failure Questionnaire (MLHFQ) [27] and by the COPD Assessment Test (CAT) [28]

Then, patients were randomized into one of the two groups. The same measurements were repeated after 4 months (T1) and after a further 2 months of follow-up (T2).

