### Outcome assessments

The primary outcome was exercise tolerance improvement measured by difference in the meters walked in the 6MWT. The secondary outcomes were: (1) reduction of hospitalizations for cardiovascular and/or respiratory diseases, (2) reduction of hospitalizations for all causes, (3) improvement of QoL in the MLHFQ and the CAT, (4) reduction in impairment/disability evaluated by the Barthel Index, (5) reduction in dyspnea evaluated by the MRC scale, (6) reduction in dyspnea and fatigue at rest evaluated by the Borg scale, (7) improvement of physical activity profile evaluated by the PASE questionnaire and daily steps reported by patients, and (8) improvement of oxygenation (PaO_2_/FiO_2_).

In the intervention group only, we also evaluated: (1) adherence to at least 70 % of the prescribed rehabilitation sessions, (2) qualitative evaluation of patients’ compliance to the rehabilitation program, (3) use of health services, calculated as total and per-person number of PT and NT scheduled and unscheduled calls, total and per-person number of PT home visits, total and per-person number of educational sessions, and total and per-person time spent by the PT and NT in the study.

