### Sample size

A priori sample size was calculated based on previously published randomized controlled trial (RCT) data on COPD and CHF rehabilitation [29, 30] using primary outcome. With an estimated improvement at T1 with respect to T0 in the treatment group of 30 ± 50 m (mean ± standard deviation (SD)) on the 6MWT and no change expected in the control group (0 ± 50 m), at 80 % of power and a significance level of *p* < 0.05, our RCT would need a sample size consisting of at least 44 participants in each group. By taking the probability of dropouts into account (20–25 % of enrolled patients), we decided to include at least 55–60 patients in each group.

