### Statistical analysis

Statistical analysis will be carried out by a certified health professional using STATA 13.0 software (College Station, TX, USA). Data will be descriptively analyzed and presented as percentage or mean ± standard deviation for all clinical variables, median ± interquartile (IQ) range for variables without a normal distribution, and percentage for categorical and binary variables. Distribution and normality of variables will be tested by the Kolmogorov-Smirnov test. To compare groups at T0, Student’s *t* test or the Mann-Whitney-Wilcoxon test for continuous variables, and the chi-squared test for categorical variables, will be used.

The effects of training will be analyzed by two-way analysis of variance (ANOVA) for repeated measures (time and group). A post hoc analysis will be conducted when the ANOVA F ratio is significant for Student’s *t* test among times and groups, and Bonferroni’s correction will be applied.

Also, predictive analysis will be performed to detect the characteristics of improvers and nonimprovers using multivariate logistic regression.

The level of significance will be set at *p* < 0.05.

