The choice of the 6MWT as a primary outcome measure was motivated by the fact that this is a very sensitive test to treatments offered in both these diseases and is among the most frequently used in the literature. The test measures the distance covered when subjects are instructed to walk as quickly as they can for 6 min, and performance on this test has been used as a measure of cardiovascular exercise capacity, particularly in patients with congestive heart failure, and chronic lung disease. The distance covered during the 6MWT has been shown to be a sensitive measure of heart disease severity and is a useful predictor of mortality [31].

We also considered it important to monitor dyspnea and muscle fatigue [23, 32] using the Borg scale; even if this is a subjective index, it gives important information on the health status of the patient at any time of the study. We chose the PASE [26] as a tool to measure the level of physical activity, as our population is aged 65 years and older. The PASE consists of self-reported occupational, household, and leisure items over a 1-week period and can be administered by telephone, mail, or in person. The PASE scoring was derived from movement counts from an electronic physical activity monitor, activity diaries, and self-assessed activity levels in a general population of noninstitutionalized older persons. The PASE can be used to measure physical activity in surveys of older people and to assess the effectiveness of interventions.

The evaluation of QoL is an important indicator of the effect of the home program and it remains poorly investigated in telehealth. Most published trials have been powered to highlight the effectiveness in “hard” endpoints such as mortality and cardiovascular or respiratory disease-related hospitalizations; consequently, information on the efficacy of such programs on surrogate outcomes, physical performance, and QoL are lacking [33, 34]. Other major indexes include patient satisfaction [35] and adherence to the program carried out [36–38], which we included in our study.

This is a real-life study, in which the complexity, frailty, age, high risk of exacerbations, and high variability in the individual response of the patients enrolled in the home program can have important effects on the expected results.

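### The three-visit repeated-measures ANOVA does not isolate the powered T1-T0 walk difference or adjust for the baseline walk, and in complete-case form it would also lose T1 walks

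*Protocol article*

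**What the plan says.** - **Outcome** (Outcome assessments): "The primary outcome was exercise tolerance improvement measured by difference in the meters walked in the 6MWT". This sentence names no visit.
- **Visits** (Trial structure): "The same measurements were repeated after 4 months (T1) and after a further 2 months of follow-up (T2". With the baseline test, Table 2 shows three walks per patient.
- **Power** (Sample size): "With an estimated improvement at T1 with respect to T0 in the treatment group of 30 ± 50 m", with "no change expected in the control group (0 ± 50 m" for controls, 80% power and a 0.05 significance level. This gives at least 44 per group. "By taking the probability of dropouts into account", put at 20-25% of enrolled patients, the target becomes 55-60 per group. The article does not say whether that loss is expected by T1 or by T2.
- **Analysis** (Statistical analysis): the training effects are to be tested by "two-way analysis of variance (ANOVA) for repeated measures (time and group". If the F ratio is significant, Bonferroni-corrected Student's t tests among times and groups follow. Stata 13.0 is the software.

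The article states no analysis set and no handling of missing walks. A condensed article may leave these to the full plan, so their absence is not part of this point.

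**The concern.** The trial was sized for one comparison, the between-group difference in T1-T0 change, tested once at 0.05. The named analysis tests time and group effects over three visits. It reaches pairwise comparisons only after a significant F ratio, and then with a multiplicity correction that the sample size does not include. The powered contrast is therefore not the one the analysis reports directly. The baseline walk enters as one of the repeated outcomes and not as a covariate, so some available precision is not used.

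The classical balanced form of this ANOVA also needs a complete T0/T1/T2 triplet. Run that way, a patient with a valid T1 walk who dies, is readmitted or withdraws before T2 would leave the T1 comparison too. The Discussion describes frail patients with a "high risk of exacerbations, and high variability in the individual response of the patients enrolled". That sentence is about variable response and not dropout, but it makes loss related to health plausible. Hospitalization is also a secondary outcome that the intervention aims to reduce, so the arms could lose different kinds of patient. Precision on the primary endpoint is at stake and, under some loss mechanisms, so is the size of the estimate.

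**Working it through.** **1. The plan's own figures.** Inputs from Sample size: difference 30 m, SD 50 m, 80% power, alpha 0.05 (sidedness is not stated; two-sided reproduces the result).

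n = 2 x 50² x (1.960 + 0.842)² / 30² = 43.6, so 44 per group. Inflation: 44/0.80 = 55 and 44/0.75 = 58.7, so 59. Both agree with the article.

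**2. What a complete-case run would cost under random loss.** Power = Φ(30 / (50 x √(2/n)) − 1.960). The timing of dropout is an assumption. Here half of it falls before T1.

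| Enrolled per arm | Total loss | Complete triplets | T1 walks | Power, completers | Power, all T1 walks | Completer SE larger by |
|---|---|---|---|---|---|---|
| 55 | 20% | 44.0 | 49.5 | 0.804 | 0.847 | 6% |
| 55 | 25% | 41.2 | 48.1 | 0.778 | 0.837 | 8% |
| 60 | 20% | 48.0 | 54.0 | 0.836 | 0.877 | 6% |
| 60 | 25% | 45.0 | 52.5 | 0.812 | 0.867 | 8% |

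If two thirds of the loss falls before T1, the SE penalty is 4-5%. If all of it does, the penalty is zero, because those patients have no T1 walk. If instead 20-25% is the loss by T1 and a further 5-10% of those enrolled are lost by T2, completer power is 0.72-0.81 against 0.78-0.84 with all T1 walks.

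**3. Adding baseline adjustment.** Assume a walk SD of 100 m and an equal correlation of 0.875 between visits. This reproduces the plan's change SD: 100 x √(2 x (1 − 0.875)) = 50 m. The residual SD after adjusting T1 for T0 is 100 x √(1 − 0.875²) = 48.4 m.

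Take 58 per arm, 10% lost before T1 (58 x 0.90 ≈ 52) and about 21% lost in total (58 x 0.79 ≈ 45.8):

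- Completers: 30/(50 x √(2/45.8)) = 2.87, power 0.82
- All T1 walks: 30/(50 x √(2/52)) = 3.06, power 0.86
- All T1 walks, baseline-adjusted: 30/(48.4 x √(2/52)) = 3.16, power 0.88

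Simulation with t tests gives 81%, 86% and 88-89%. All three estimates centre on 30 m.

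**4. Loss related to outcome (simulated, true effect 30 m).** Same setting, but loss after T1 has a base rate of 10% (intervention) and 15% (control), with odds rising for a worse T1 change.

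- Odds x1.65 per 50 m worse: completers about 28 m, power about 77%.
- Odds x2.7 per 50 m worse: completers about 26 m, power about 71%.
- All T1 walks: 30 m in both cases, because the 10% lost before T1 was random by assumption.

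If loss before T1 is also made to depend on outcome, the baseline-adjusted analysis of all T1 walks is biased as well. It gives about 28-29 m under the weaker dependence and 26-28 m under the stronger, varying with how the early loss is set up.

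**5. Does the named method force deletion?** In one simulated trial of 60 per group with 28 patients missing T2, a long-format repeated-measures ANOVA (subject, time, group x time) kept every T1 walk. Its T1 contrast was 38.0 m (SE 8.3), identical to the simple difference in everyone with a T1 walk. Listwise deletion on the same data gave 44.8 m (SE 9.0). Both can be described as a two-way repeated-measures ANOVA.

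**The case against.** The strongest reply is that the article names only a method. It mentions no listwise deletion, and Stata can fit the ANOVA in long format and keep patients with T0 and T1 only. Nothing in the post hoc step requires a T2 value for a T1 comparison. The inflation from 44 to 55-60 already treats dropouts as contributing nothing, so a completer analysis keeps about 78-84% power at the stated dropout. Analysis set and missing-data rules may sit in a fuller plan.

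Most of this stands. A reader might infer that the plan discards T1 data and so makes the primary comparison a biased completer analysis. The documents do not support that. Deletion depends on implementation, dropout timing is not given, and random loss produces no bias. The direction of any bias also depends on which patients leave which arm, and the preferred analysis shares any bias from outcome-related loss before T1. A reader might also infer an inflated type I error from unequal visit spacing through a failure of sphericity. That would need the variance of the T1-T2 change, which the article does not give, so no figure is claimed.

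Two things survive. The named analysis does not isolate the contrast that was powered, whichever way incomplete patients are handled. And the inflated sample size protects precision only, not the estimate if loss is related to outcome.

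**Conclusion.** The point holds as a mismatch between the analysis and the powered contrast, with a conditional risk of losing T1 data. It is a worthwhile improvement and not a fatal flaw. Under random loss and the step 3 assumptions, keeping all T1 walks is worth about 5 power points over completers, and baseline adjustment adds 2-3 more. At the article's own 20-25% dropout, the gain from keeping T1 walks runs from 0 to about 6 points, depending on timing. Bias arises only if loss is related to outcome. Where loss after T1 follows poor T1 change and the analysis is run on completers, a true 30 m is estimated at about 26-28 m. The walk SD of 100 m, the correlation of 0.875, the timing split and the loss models are assumptions. Only the 30 m effect, the 50 m change SD, the 20-25% dropout and the 44 and 55-60 per group come from the article.

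**What to change.** Name the T1 between-group difference in 6MWT as the primary contrast. Estimate it in all patients as randomized with available walks, by one of:

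- a likelihood-based mixed model with arm x visit, the T0 walk as covariate or a constrained baseline, unstructured covariance and centre, reading off the T1 contrast; or
- an ANCOVA of the T1 walk on arm, T0 walk and centre.

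Report the T2 contrast as secondary. Add one sensitivity analysis for patients who died or were too ill to walk, for example by giving them the worst rank, because outcome-related loss before T1 would bias the primary model too.

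The cost is analysis wording, a standard Stata command and slightly more model specification. No new data are needed. Trial status reports that follow-up has ended and data are being processed, so the change should be fixed and dated before results by arm are seen.

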## Discussion

With the progressive ageing of the general population, there is a need to develop more intensive and integrated rehabilitation interventions for the growing number of more complicated, disabled, high-risk patients. The aim of our study was to provide patients with combined COPD/CHF (complex and frequently frail patients with a very high risk of rehospitalization) with an integrated, multidisciplinary NT- and PT-oriented program at the time of in-hospital rehabilitation discharge. This would be characterized by improved knowledge of the signs and symptoms of their disease, with interventions on self-management in the use of medications, evaluation and solution of problems related to exacerbations according to a personalized action plan (self-management), continuous education at a distance with the possible use of a specialist network for a second opinion via remote surveillance (self-guided), home visits as needed, and a guided rehabilitation maintenance program (home care).

Despite the increasing incidence of chronic diseases and, among them, the high prevalence of CHF and COPD, there are no studies in the literature dealing with a similar home-care approach supported by telemedicine in this patient population, where the coexistence of both diseases implies a far greater functional deficit and impact on QoL than in other chronic conditions. Through this program, the NT and PT, with the support of the physician, actively monitored the clinical situation and the patient’s physical status, modifying the therapeutic approach and the workload weekly.

To minimize bias we used consecutive enrollment and central randomization. Due to the nature of the trial it was not possible to blind patients and health care personnel. We tried to standardize as much as possible the nursing and physiotherapy approach in the three hospitals involved in patient enrollment, conducting joint training of staff, organizational meetings and planning before commencing patient enrollment. The rehabilitation program adopted at home tried to reproduce as much as possible the rehabilitation carried out in the hospital, at the same time personalizing the program to the needs of patients.

The choice of the 6MWT as a primary outcome measure was motivated by the fact that this is a very sensitive test to treatments offered in both these diseases and is among the most frequently used in the literature. The test measures the distance covered when subjects are instructed to walk as quickly as they can for 6 min, and performance on this test has been used as a measure of cardiovascular exercise capacity, particularly in patients with congestive heart failure, and chronic lung disease. The distance covered during the 6MWT has been shown to be a sensitive measure of heart disease severity and is a useful predictor of mortality [31].

We also considered it important to monitor dyspnea and muscle fatigue [23, 32] using the Borg scale; even if this is a subjective index, it gives important information on the health status of the patient at any time of the study. We chose the PASE [26] as a tool to measure the level of physical activity, as our population is aged 65 years and older. The PASE consists of self-reported occupational, household, and leisure items over a 1-week period and can be administered by telephone, mail, or in person. The PASE scoring was derived from movement counts from an electronic physical activity monitor, activity diaries, and self-assessed activity levels in a general population of noninstitutionalized older persons. The PASE can be used to measure physical activity in surveys of older people and to assess the effectiveness of interventions.

The evaluation of QoL is an important indicator of the effect of the home program and it remains poorly investigated in telehealth. Most published trials have been powered to highlight the effectiveness in “hard” endpoints such as mortality and cardiovascular or respiratory disease-related hospitalizations; consequently, information on the efficacy of such programs on surrogate outcomes, physical performance, and QoL are lacking [33, 34]. Other major indexes include patient satisfaction [35] and adherence to the program carried out [36–38], which we included in our study.

This is a real-life study, in which the complexity, frailty, age, high risk of exacerbations, and high variability in the individual response of the patients enrolled in the home program can have important effects on the expected results.

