### Study sites and patient population

Patients were recruited consecutively from the Cardiology and Pulmonary Departments of three rehabilitation hospitals in Italy (Salvatore Maugeri Foundation IRCCS Institutes of Lumezzane and Montescano; and San Raffaele Pisana IRCCS, Rome). Patient selection criteria are listed in Table 1. CHF and COPD diagnoses had to be documented from at least one echocardiogram (CHF) performed within the previous 12 months under clinically stable conditions [21] and by a spirometry examination (COPD) [6] performed within the previous 12 months.

**Table 1 Tab1:** Eligibility criteria

Inclusion criteria	Exclusion criteria
1. Age over 18 years	Physical activity limitations due to noncardiac and/or pulmonary conditions
2. Chronic obstructive pulmonary disease (COPD) GOLD classification (classes B, C, and D) [11]	Limited life expectancy
3. Systolic and/or diastolic heart failure (HF) New York Heart Association (NYHA) classes II, II, and IV	Severe cognitive impairments
4. At least one hospitalization or visit due to HF or COPD exacerbation in the previous 12 months	
5. Signed informed consent	

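### Change in PASE from a pre-discharge T0 mixes the return home with training, so the PASE conclusion should rest on the between-arm difference at T1 and T2, adjusted for T0

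*Protocol article*

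**What the plan says.** **Instrument.** The Discussion of the protocol article says: "The PASE consists of self-reported occupational, household, and leisure items over a 1-week period". It adds that the scoring drew on, among other sources, "self-assessed activity levels in a general population of noninstitutionalized older persons".

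**Timing.** Under Trial structure: "Before discharge from hospital to home (T0), all candidates underwent assessment". Table 2 labels the T0 column "Baseline (before discharge" and schedules PASE at T0, T1 (4 months) and T2 (a further 2 months). Randomization follows the T0 assessments. Under Rehabilitation program, home training generally began 7 days after enrollment, once the patient had been discharged. The Control group section shows that control patients were discharged home too.

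**Outcome and analysis.** Item 7 of the eight secondary outcomes includes "improvement of physical activity profile evaluated by the PASE questionnaire". The Statistical analysis section assigns training effects to a repeated-measures ANOVA with factors time and group. Bonferroni-corrected t tests among times and groups follow when the F ratio is significant. It does not say which F ratio opens these tests.

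**Age.** The Discussion justifies PASE "as our population is aged 65 years and older". The first inclusion criterion in Table 1 is "Age over 18 years".

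**The concern.** A one-week recall of household, work and leisure activity means something different in a rehabilitation ward than at home. Household and occupational items hardly apply to an inpatient, and the article itself ties the scoring to people living outside institutions. A rise in PASE between T0 and T1 may therefore reflect discharge in either arm, with or without training.

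Two things are at stake. First, the outcome is worded as an improvement and the plan allows tests among times, so a significant within-arm rise could be reported as a benefit of the program. Bonferroni correction controls the number of tests. It does not separate discharge from training. Second, if the inpatient score says little about activity at home, subtracting it adds noise to the between-arm comparison.

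**Working it through.** **1. Which week does T0 cover?** If T0 falls just before discharge, and discharge is about 7 days after enrollment, the recall week is an inpatient week. If T0 falls nearer enrollment, some recall days may precede admission, because weekly screening looked for patients admitted in the previous week. Length of stay is not stated. The article fixes a recall period for the Borg scale (the day before) but no special one for PASE at T0. Mainly inpatient days is therefore the probable reading, not a certain one.

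**2. Inputs for the arithmetic.** The article gives no PASE mean, SD, correlation or target difference. Its only design figure concerns the 6MWT and reproduces: 2 × [50 × (1.960 + 0.842)/30]² = 43.6, hence 44 per group; 44/0.80 = 55 and 44/0.75 = 58.7, hence 55 to 59 against the stated 55–60. I use 44 per arm below. Everything else is assumed. PASE is in units of SD(T1), S is a shift common to both arms on going home, and E is the true between-arm effect.

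**3. Between-arm bias.** The expected T0-to-T1 change is S + E in the intervention arm and S in the control arm. The difference is E, so S cancels. In 4,000 simulated trials per setting (44 per arm, r = 0.3, E = 0), the between-arm test of change rejected in 0.053, 0.053 and 0.048 of trials for S = 0, 0.5 and 1.0.

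**4. Within-arm tests.** With E = 0 and equal SDs, the probability that one arm's change is significant at 0.05 (before Bonferroni) is about Φ(S√44/√(2(1 − r)) − 1.96). For S = 0.5:
- r = 0: Φ(2.345 − 1.96) = 0.65
- r = 0.3: Φ(2.803 − 1.96) = 0.80
- r = 0.6: Φ(3.708 − 1.96) = 0.96

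For S = 1.0 it is at least 0.997. These probabilities apply to each arm, including control.

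**5. Precision.** Set Var(T1) = 1, SD(T0) = k and correlation r.
- Change: 1 + k² − 2kr
- T1 alone: 1
- T1 adjusted for T0 (large samples): 1 − r²

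| Variance relative to T1 alone | r = 0 | r = 0.2 | r = 0.4 |
|---|---|---|---|
| Change, k = 1 | 2.00 | 1.60 | 1.20 |
| Change, k = 0.5 | 1.25 | 1.05 | 0.85 |
| Adjusted for T0, any k | 1.00 | 0.96 | 0.84 |

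Change is less precise than T1 alone only when r < k/2. Change minus adjusted is 1 + k² − 2kr − (1 − r²) = (k − r)², which is never negative. In large samples the adjusted analysis is therefore at least as precise as change whatever k is, and at least as precise as T1 alone.

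**6. Power, equal SDs (k = 1), E = 0.5, 44 per arm.** Power is about Φ(0.5/(s√(2/44)) − 1.96), with s the square root of the relative variance. For change it is 0.38, 0.51 and 0.75 at r = 0, 0.3 and 0.6. For T1 alone it is 0.65. Adjusted for T0 it is 0.65, 0.69 and 0.83.

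**The case against.** The strongest reply is that the trial compares two randomized arms. T0 precedes randomization and both arms go home, so a common shift drops out of time by group. That stands. A reader might infer that PASE improvement in this trial simply measures discharge. This is true at most of within-arm change and the time effect, and the article nowhere says that PASE will be judged within arm.

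A reader might also infer that a significant time effect is practically assured. The documents do not support that, since the size of the shift is unknown. Patients were exercising in hospital, and the home program was meant to resemble the hospital one. Even an assumed 0.5 SD shift gives only 0.65 at r = 0, before Bonferroni.

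A doubled variance is likewise the extreme of the range considered. It needs equal SDs and zero correlation. If the inpatient week flattens activity, T0 scores should vary less. At k = 0.5 the ratio is 1.25 at r = 0, and at r = 0.4 it falls below 1. This stands, and the loss can only be given as a range.

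Finally, PASE is half of one secondary outcome among eight, tests between groups are already foreseen, and covariate adjustment is often left to an analysis plan not shown here. That limits the weight of the point. It does not remove it, because the article does fix tests among times, and these are exposed to the change of setting.

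On age, the Discussion may describe the patients actually enrolled while Table 1 sets a floor. It cannot be inferred that PASE was used in many patients under 65, and the age statement has no bearing on the discharge question.

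**Conclusion.** The point holds in limited form. The randomized PASE contrast is not biased by a discharge shift common to both arms. The time effect and within-arm changes from T0 cannot be read as training effects. Using change from T0 costs anywhere from nothing to a doubling of variance relative to T1 alone, for k up to 1 and r of 0 or more; the documents do not allow a narrower figure. This rests on the T0 recall window being mainly inpatient, which is probable from the schedule but not stated. The consequence is confined to a secondary outcome and leaves the 6MWT sample size untouched. The age statement is a separate, minor inconsistency.

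**What to change.** Base the PASE conclusion on the between-arm difference at T1 and at T2, with T0 PASE as a covariate. Do not present within-arm change from T0, or the ANOVA time effect, as an effect of training. When reporting, state the recall instruction that was used at T0.

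Separately, reconcile the sentence on age in the Discussion with Table 1. A repeat analysis restricted to patients aged 65 or over is needed only if younger patients were enrolled.

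The cost is small. The data are already collected, as follow-up had ended and the article reports them as being processed, so only analysis wording and one model change. The downside is that PASE loses its change-from-baseline headline.
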